**Group Dialectical Behavioural Therapy for Mood Instability within Bipolar Disorder: An Open Trial**

**Study Protocol**

**Summary**

Background

Bipolar Disorders (BD), including all types, affects around 4-5% of the population. BD typically follow a relapsing course and are associated with considerable economic burden, estimated in 2002 at £2 billion annually in the UK (Das Gupta & Guest, 2002). BD are also associated with high personal and social costs, including a suicide rate that has been conservatively estimated at 9 times that of the general population (Dutta et al., 2007), and exceeds that associated with unipolar depression. Medication is generally considered to be the first line of treatment for individuals with BD (NIHCE, 2006) however a substantial number of individuals with BD continue to relapse despite use of medication (Gitlin et al., 1995). Furthermore, ongoing mood instability outside of full episodes is a significant difficulty experienced by many individuals with BD. This can range from residual mood symptoms between episodes of Bipolar I Disorder (which appear to affect over half of those with BD-I: Keitner et al., 1996) to the persistent short-lived swings in mood that characterise cyclothymia. As well as being distressing and destabilising, there is evidence that residual symptoms predict a worse course of BD (Benazzi, 2001; Judd et al., 2008) whilst those with cyclothymia have a greater likelihood of developing Bipolar I or II Disorder (Alloy et al., 2012).

Whilst there is evidence to suggest that certain psychological therapies (such as Cognitive Behavioural Therapy and group Psychoeducation) can be helpful in reducing risk of relapse and / or reduce symptoms of acute and residual bipolar depression, there are no evidence-based psychological therapies available for individuals experiencing ongoing mood instability, defined as either frequent sub-clinical shifts in mood outside of full episodes, or cyclothymic mood swings.

Dialectical Behaviour Therapy (DBT) was developed by Marsha Linehan as an approach for individuals with Borderline Personality Disorder (Linehan, 1993) and is recommended in the NICE clinical guideline for Borderline Personality Disorder (Department of Health, 2009). Since the initial development of DBT, studies have found it to be efficacious in other patient groups including individuals with substance use problems and those with treatment resistant depression. DBT aims to give individuals who experience rapid and intense shifts in affect skills for managing this, both in terms of their responses to shifts in affect, and in terms of shaping their environments in ways that promote emotional stability. DBT aims to help the client both to accept the realities of their situation and responses, and to make changes where it would be helpful. Traditional DBT consists of group-based skills training alongside individual therapy sessions, with therapist contact calls allowing generalisation of the skills learned into the client’s daily life.

Bipolar Disorders and Borderline Personality Disorder, whilst differing in a number of ways, share some common hypothesised underpinning processes, including elevated reward sensitivity and difficulties in emotion regulation. In addition, both disorders often involve rapid and extreme changes in affect. Despite this phenomenological and theoretical overlap there has little research evaluating DBT for BD. An open trial and a pilot randomised controlled trial have evaluated individual and family-based skills training for adolescents with BD (Goldstein et al., 2014; Goldstein, Axelson, Birmaher & Brent, 2007), whilst one pilot randomised controlled trial has investigated group-based DBT skills training for adults with BD (Van Dijk, Jeffrey & Katz, 2013). No studies to date have specifically investigated this approach as a means to help individuals with ongoing bipolar mood instability; rather, studies to date have included participants on the basis that they experience episodes of BD, regardless of whether or not their mood is stable between episodes. In the absence of evidence based psychological therapies for this group, DBT would appear to be a credible approach both in terms of target symptomatology and underpinning theory, and one which can be delivered in a group format reducing costs and potentially combatting social isolation and internalised stigmatisation.

We have developed a protocol for group-based DBT training that draws upon theoretical and empirical work into basic processes in Bipolar Disorder to adapt standard DBT for this client group. The format of the group is designed to make this intervention feasible to deliver within outpatient primary or secondary mental health settings whilst allowing for individualisation and generalisation of skills through individual skills-coaching sessions and the use of a mobile phone application (Rizvi et al., 2011).

Study Aims and Hypotheses

The aim of this study is to formally evaluate group DBT skills training for individuals with ongoing bipolar mood instability (frequent mood swings that persist outside of – or instead of - full episodes of illness). This will provide information that can be used to further refine the content and delivery of the intervention and inform the design of a pilot randomised controlled trial of the intervention.

Evaluation will primarily focus upon:

1. The feasibility and acceptability to participants and referring clinicians of i) the content of the intervention; ii) the delivery of the intervention (in terms of group and individual components, the “open” nature of the group element, and the use of experience sampling to support therapy).
2. Testing key outcome variables observed in participants in the group.
3. Evidence for mechanisms of change within participants in the group.

Hypotheses:

1. The intervention will be both feasible and acceptable to participants, clinicians and refers as measured through uptake and adherence rates, and qualitative feedback.
2. Between the baseline assessment and the end of the group participants will show i) a trend of decreasing levels of depressive and manic symptoms; ii) decreases in variability of symptoms and day-to-day mood; iii) increases in quality of life and sense of personal recovery.
3. The above changes will be i) associated with; ii) preceded by increases in mindfulness and group fit, and decreases in behavioural avoidance, positive and negative urgency, impulsivity and problematic beliefs about extreme mood states.

Experimental Design and Methods

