**Method**

*Participants*

Participants will be up to 16 individuals recruited through the Mental Health Assessment Team in the Exeter and East Devon area, and in the Mid Devon area if necessary.

In addition we will invite at least four members of staff from referring services to provide data on the acceptability of the Thrive programme.

Inclusion criteria for patient participants are: i) aged 18 or over; i) meets DSM-V criteria for Bipolar Spectrum Disorder; iii) current bipolar mood instability (over the past two years numerous periods with hypomanic symptoms that do not meet criteria for a hypomanic episode and numerous periods with depressive symptoms that do not meet criteria for a depressive episode, continuing into the past month); iv) client wishes to engage in psychological therapy that focusses primarily on ongoing mood instability and its consequences.

Exclusion criteria are: i) current substance dependence disorder; ii) currently receiving other psychological therapy; iii) the patient is currently actively suicidal; iv) presenting difficulties that are characteristic of Borderline Personality Disorder rather than Bipolar Disorder and that would be an early treatment target in standard DBT (frequent and serious deliberate self-harm, marked disturbance in ability to form or maintain interpersonal relationships); v) presence of another area of difficulty that the therapist and client believe should be the primary focus of intervention (for example panic disorder with agoraphobia, Post Traumatic Stress Disorder); vi) the information available suggests that the person may present a significant risk to other group members (such as aggression, likelihood of carrying out sexual or other exploitation); vii) the person lacks capacity to consent to treatment or research participation; viii) currently experiencing an episode of mania.

Inclusion criteria for staff participants are: i) mental health professional working within a service that can refer patients to the study.

*Materials*

Structured Clinical Interview for DSM-IV (SCID V: First, Williams, Karg & Spitzer, 2015): This is a clinician rated semi-structured interview for ascertaining diagnostic status according to the Diagnostic and Statistical Manual for Mental Disorders (DSM-IV: American Psychiatric Association, 2000) and is the gold standard for obtaining a diagnosis for research purposes.

*Outcome Measures*

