Bech Mania Rating Scale (BMRS: Bech, Rafaelson, Kramp & Bolwig, 1978): An 11 item observer rated instrument, with higher scores corresponding to higher levels of hypomania or mania. This scale has been shown to have good internal consistency and construct validity.

Altman Scale for Rating Mania (ASRM: Altman, Hedeker, Peterson & Davis, 1997): A five item self-report measure of current manic symptom level that has been validated in patient populations .

The Bipolar Disorder Recovery Questionnaire (BDRQ: Jones, Mulligan, Higginson, Dunn & Morrison, 2013): A 36 item self-report measure that has been developed to measure personal recovery in people with Bipolar Disorder, as distinct from symptomatic or medical recovery. The BDRQ has been found to have adequate internal consistency and convergent validity.

The Brief Quality of Life in Bipolar Disorder scale (QoL.BD: Michalak & Murray, 2010): This is a 12 item self-report measure of quality of life that has been specifically designed for and validated with individuals with Bipolar Disorder.

Acceptability Questionnaires: Before starting the programme, participants will be asked about the extent to which they find it acceptable, and their general views on being offered a group treatment, as will referring clinicians. After completing the group participants and clinicians will be asked about their experience of the programme. The questionnaires contain both qualitative and quantitative elements, and includes questions about the smartphone app, based on a measure used in a previous published study (Rizvi et al., 2011).

Experience Sampling Measure (ESM):

Participants in the group will make use of a mobile phone application (“app”) which has been purpose designed by the experimenter for use in this study. This application alerts the individual 5 times per day over a period of 7 days. On each occasion the user is asked to rate his / her mood on a scale of -10 to +10. They are also asked if they have done anything since the last alert deliberately to regulate their mood, and if so, the extent to which this was helpful. This app will be used at the start and the end of the study to measure within and between day fluctuations in mood, and use of helpful coping responses.

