Patient participants will be identified by staff members in the xxxxxxx Mental Health Assessment Team (with the xxxxxxx Assessment Team being a second possible recruitment source if necessary) on receipt of referrals of individuals with Bipolar Disorder. If necessary we will also recruit from Recovery services (secondary mental health teams) in Exeter. Participants likely to meet study criteria will be informed about the study by the assessing staff member during a routine assessment appointment (given Participant Information Sheet). If necessary the patient and / or staff member can liaise with the research team to address questions about the study and study eligibility that arise at this stage. Patients expressing an interest in the study will then be referred to the AccEPT service, which hosts the project. Once referred, potential participants will be contacted to explain the study, have an opportunity to answer questions, and arrange an assessment appointment if they wish to proceed. At the assessment appointment the researcher will explain the study further, address questions and take informed consent. Following this the researcher will ascertain whether the participant meets study inclusion / exclusion criteria (the SCID will be used to investigate criteria pertaining to diagnosis). If the participant is not eligible for the study this will be explained and the participant referred onwards as appropriate. If the participant is eligible he / she will be invited to complete the “outcome” and “process” measures listed above, in addition to the standard assessment measures used within the AccEPT service. This can be done in the University or at home, in accordance with the participant’s preference. The participant will also be asked to complete the ESM recording period for a week prior to starting the group. He / she will be instructed in the use of the app at the end of the assessment session.

Participants will then undertake treatment as per the usual procedures at the AccEPT service; this involves completing measures of symptoms (ASRM and BDI-II) at each session. To this we will add the single item measure of group fit, and a single visual analogue scale of mood that day (from -10 to +10).

In addition participants will complete the following measures half way through the group cycle: UPPS-P, KIMS, BADS, HAPPI, IIP-32.

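### Hypothesis 2(ii) predicts a fall in symptom variability from baseline, but only one pre-treatment administration of the symptom scales is scheduled, so baseline symptom variability cannot be estimated

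*Protocol*

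**What the plan says.** Study Aims and Hypotheses sets the interval for all of hypothesis 2: "Between the baseline assessment and the end of the group participants will show" the listed changes. Part (ii) names two quantities: "ii) decreases in variability of symptoms and day-to-day mood". Part (i) separately predicts falling levels of depressive and manic symptoms.

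The Procedure section sets the schedule. At assessment, eligible participants complete the outcome and process "measures listed above, in addition to the standard assessment measures used within the AccEPT service". No repeat before treatment is stated. The serial symptom scores belong to the treatment phase: "this involves completing measures of symptoms (ASRM and BDI-II) at each session". A single mood rating from -10 to +10 is added at those same sessions.

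The one repeated measurement before treatment is the app: "The participant will also be asked to complete the ESM recording period for a week prior to starting the group". Under Experience Sampling Measure, "This application alerts the individual 5 times per day over a period of 7 days", and "On each occasion the user is asked to rate his / her mood on a scale of -10 to +10". The app also asks about deliberate mood regulation but carries no depressive or manic symptom scale. It is used in this form at the start and the end of the study.

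Statistical Analysis plans Wilcoxon signed rank tests of mean change for the questionnaires, mixed modelling of the app data, and individual-level trend analysis.

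**The concern.** A change in variability needs an estimate of variability at both ends of the interval. For symptoms, the schedule supplies a series at the late end only. If the analysis substitutes early sessions for baseline, participants are already in treatment when those scores are taken, and the result no longer answers hypothesis 2(ii).

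The substitute also has a built-in bias. If symptom levels fall across the early sessions, as part (i) predicts, that fall itself adds to the raw spread of the early scores. Variability could then appear to decrease when only the level has changed.

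This matters because mood instability is the condition under study and an entry criterion, the trial has no control group, hypothesis 3 builds on the changes named in hypothesis 2, and the results are meant to inform a pilot randomised trial. A statistical analysis plan could define a variability statistic, but it could not supply scores that were never collected.

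**Working it through.** **Plan's own figure.** Statistical Analysis gives about 560 app ratings: 16 persons × 5 per day × 7 days = 560, which reproduces. This is one 7-day window. Per person it is 5 × 7 = 35 ratings, and the start and end windows together give at most 2 × 560 = 1,120.

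**Count of pre-treatment measurements per person (Procedure; Outcome Measures).**

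| Quantity in 2(ii) | Before the group | At the end | Baseline variability estimable? |
|---|---|---|---|
| Day-to-day mood (app) | up to 35 ratings in one week | up to 35 ratings in one week | Yes |
| Symptoms (ASRM, BDI-II) | one stated administration | series from the later sessions | No |

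BDI-II is not in the protocol's list of outcome measures. Its assessment score is presumed to come from the clinic's standard measures, which are not itemised.

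**Precision of a within-person SD from k scores.** Assuming independent normal scores, the 95% limits are the estimate multiplied by √[(k−1)/χ²(0.975, k−1)] and √[(k−1)/χ²(0.025, k−1)].

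| k | Lower multiplier | Upper multiplier |
|---|---|---|
| 1 | none (0 df) | none (0 df) |
| 2 | 0.45 | 31.9 |
| 4 | 0.57 | 3.73 |
| 8 | 0.66 | 2.04 |
| 35 | 0.81 | 1.31 |

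The row k = 2 is the most generous reading, in which the session 1 form counts as pre-treatment. The row k = 35 is the app week; its limits widen with autocorrelation.

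As an approximate relative standard error, 1/√[2(k−1)]: for k = 4, 1/√6 = 0.41; for k = 8, 1/√14 = 0.27.

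**Effect of a falling level on the raw SD.** Suppose a person's scores fall by b points per session with independent scatter of SD s around that line. Over four sessions the sample variance of 1, 2, 3, 4 is 5/3, so the expected raw variance is s² + (5/3)b². With no scatter at all (s = 0), the raw SD is √(5/3) × b = 1.29b. If the level has flattened by the last sessions (b near 0), the raw SD falls even with s unchanged. Spread around the person's own fitted line removes this, at the cost of one more degree of freedom: relative error 1/√[2(k−2)], which is 1/√4 = 0.50 for k = 4 and 1/√12 = 0.29 for k = 8.

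**The case against.** The strongest reply is that the session series has a purpose of its own. The ethics section on the intervention reports an earlier service evaluation that looked at stability of depressive symptoms from the start to the end of two groups, and Statistical Analysis plans individual trend analysis over time. Early-versus-late variability can be estimated from up to 16 sessions, and choosing the statistic is normal work for an analysis plan. The stakes are also modest: the trial is uncontrolled, feasibility and acceptability come first among its aims, and no decision rule hangs on 2(ii). All of this stands. It limits the point to the stated interval and its wording, but it does not supply a baseline series.

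A reader might go further and infer that the app week is too short, because eligibility refers to "over the past two years numerous periods with hypomanic symptoms". The protocol does not support that. Two years is the look-back window for eligibility, not the length of a swing. The Background, the study aims and the section on potential benefits describe the target as brief, frequent or rapid changes. The app is meant for fluctuation within and between days, and it is run before and after treatment. The day-to-day mood half of 2(ii) is therefore unaffected. The app fails to fill the symptom gap because it records mood, and the hypothesis lists symptoms separately.

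It is also fair to object that a long run-in cannot be assumed. Apart from the app week, the protocol gives no interval between assessment and session 1, and replacement participants join at the start of the next module. Four weekly scores may be out of reach for some people.

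**Conclusion.** The point holds for the symptom half of hypothesis 2(ii) only. From the baseline assessment to the end of the group, change in within-person symptom variability cannot be estimated: one stated administration gives 0 degrees of freedom. Even with session 1 counted as baseline, there is 1 degree of freedom and an upper limit of about 32 times the estimate. The first result needs no assumption beyond reading the Procedure as written, with no unlisted repeat before treatment. The second assumes independent normal scores.

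This does not mean that symptom variability cannot be studied at all. Change across the treatment period is estimable, provided that it is labelled as such and the trend in level is removed. The defect is a mismatch between hypothesis and schedule. It is worth correcting because otherwise a comparison made within treatment may be reported as change from baseline.

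**What to change.** Restate 2(ii) as two contrasts.

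- **Mood:** variability in the app week before the group against the app week at the end.
- **Symptoms:** variability over the first sessions against the same number of last sessions, measured as spread around each person's own trend and not described as change from baseline. Fix the number of sessions in advance; with 16 sessions, the largest non-overlapping windows are eight each.

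This is a change of wording and costs nothing.

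Where the wait before session 1 allows, also collect ASRM, BDI-II and the -10 to +10 rating weekly at home from the assessment. Report pre-group against final-session variability, with equal numbers of scores, as a secondary and imprecise estimate. With four scores, each person's SD has about 41% relative error, or about 50% if a line is fitted, assuming independent normal scores. Questionnaires may already be completed at home at baseline, so no extra visits or participants are needed. The downside is slight participant burden, and few or no pre-group scores for people who start quickly; report how many contribute.

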**Design**

Open (uncontrolled) trial.

**Method**

*Participants*

Participants will be up to 16 individuals recruited through the Mental Health Assessment Team in the Exeter and East Devon area, and in the Mid Devon area if necessary.

In addition we will invite at least four members of staff from referring services to provide data on the acceptability of the Thrive programme.

Inclusion criteria for patient participants are: i) aged 18 or over; i) meets DSM-V criteria for Bipolar Spectrum Disorder; iii) current bipolar mood instability (over the past two years numerous periods with hypomanic symptoms that do not meet criteria for a hypomanic episode and numerous periods with depressive symptoms that do not meet criteria for a depressive episode, continuing into the past month); iv) client wishes to engage in psychological therapy that focusses primarily on ongoing mood instability and its consequences.

Exclusion criteria are: i) current substance dependence disorder; ii) currently receiving other psychological therapy; iii) the patient is currently actively suicidal; iv) presenting difficulties that are characteristic of Borderline Personality Disorder rather than Bipolar Disorder and that would be an early treatment target in standard DBT (frequent and serious deliberate self-harm, marked disturbance in ability to form or maintain interpersonal relationships); v) presence of another area of difficulty that the therapist and client believe should be the primary focus of intervention (for example panic disorder with agoraphobia, Post Traumatic Stress Disorder); vi) the information available suggests that the person may present a significant risk to other group members (such as aggression, likelihood of carrying out sexual or other exploitation); vii) the person lacks capacity to consent to treatment or research participation; viii) currently experiencing an episode of mania.

Inclusion criteria for staff participants are: i) mental health professional working within a service that can refer patients to the study.

*Materials*

Structured Clinical Interview for DSM-IV (SCID V: First, Williams, Karg & Spitzer, 2015): This is a clinician rated semi-structured interview for ascertaining diagnostic status according to the Diagnostic and Statistical Manual for Mental Disorders (DSM-IV: American Psychiatric Association, 2000) and is the gold standard for obtaining a diagnosis for research purposes.

*Outcome Measures*

Bech Mania Rating Scale (BMRS: Bech, Rafaelson, Kramp & Bolwig, 1978): An 11 item observer rated instrument, with higher scores corresponding to higher levels of hypomania or mania. This scale has been shown to have good internal consistency and construct validity.

Altman Scale for Rating Mania (ASRM: Altman, Hedeker, Peterson & Davis, 1997): A five item self-report measure of current manic symptom level that has been validated in patient populations .

The Bipolar Disorder Recovery Questionnaire (BDRQ: Jones, Mulligan, Higginson, Dunn & Morrison, 2013): A 36 item self-report measure that has been developed to measure personal recovery in people with Bipolar Disorder, as distinct from symptomatic or medical recovery. The BDRQ has been found to have adequate internal consistency and convergent validity.

The Brief Quality of Life in Bipolar Disorder scale (QoL.BD: Michalak & Murray, 2010): This is a 12 item self-report measure of quality of life that has been specifically designed for and validated with individuals with Bipolar Disorder.

Acceptability Questionnaires: Before starting the programme, participants will be asked about the extent to which they find it acceptable, and their general views on being offered a group treatment, as will referring clinicians. After completing the group participants and clinicians will be asked about their experience of the programme. The questionnaires contain both qualitative and quantitative elements, and includes questions about the smartphone app, based on a measure used in a previous published study (Rizvi et al., 2011).

Experience Sampling Measure (ESM):

Participants in the group will make use of a mobile phone application (“app”) which has been purpose designed by the experimenter for use in this study. This application alerts the individual 5 times per day over a period of 7 days. On each occasion the user is asked to rate his / her mood on a scale of -10 to +10. They are also asked if they have done anything since the last alert deliberately to regulate their mood, and if so, the extent to which this was helpful. This app will be used at the start and the end of the study to measure within and between day fluctuations in mood, and use of helpful coping responses.

During the group itself participants will continue to use the app, however during this phase it will be modified in order that it can be used therapeutically. Participants are asked to specify a “cut-off” at either end of the mood scale, and can determine the number of alerts they wish to receive per day. When the alert sounds they are asked to rate their mood as previously. If they rate themselves above their upper threshold (or below their lower one) they will be informed of this by the app and will be presented with recommendations (typically these will be skills learned in the group: participants can select their own recommendations in advance and programme them into the app). This means of using the app is intended to enhance the therapeutic efficacy of the group by helping participants to generalise the skills learned into everyday life at the times they are most needed. Participants will be able either to run the app on their own smartphone (if this is an android device) or will be able to borrow a device from the researchers (this will not be connected to the internet or be able to make calls). Data is returned to researchers either through downloading to the researchers’ PC directly from the device (if it is a University-owned device), or by the application sending anonymous data by email to the researchers’ server (if it is the participant’s own device).

*Process Measures:*

The UPPS-P Impulsive Behaviour Scale (Whiteside, Lynam, Miller & Reynold, 2005): A 59 item self-report measure that assesses five subscales (urgency, premeditation, perseverance, sensation seeking, and positive urgency) that are used to measure five distinct dimensions of impulse behaviour. This measure is included as a core proposed mechanism of action for DBT is via reduction of impulsive response to emotion.

The Behavioural Avoidance in Depression Scale (BADS: Kanter, Mulick, Busch, Berlin & Martell, 2007): A 25 item self report measure of avoidance behaviour and the impact of this upon social and daily functioning. This measure is included as our adaptations to the standard DBT protocol include an increased focus upon behavioural responses to emotion that exacerbate depression, specifically avoidance behaviours.

Kentucky Inventory of Mindfulness Skills (KIMS: Baer, Smith & Allen, 2004): A 39-item self-report inventory covering four facets of mindfulness: observing, describing, acting with awareness, and accepting without judgment. The KIMS is included as increase in mindful awareness and action are key hypothesised mechanisms by which DBT brings about more adaptive responses to ones emotions.

Group Fit Item: This asks participants to rate their sense of “fit” with the group on a single-item pictorial scale. This will be used to investigate whether there may be a relationship between a patient’s sense of fit with the group and his or her outcomes, as evidence suggests that social identification with treatment group may predict reduction of depression symptoms in individuals with Unipolar Depression (Cruwys et al., 2014).

Brief Hypomanic Attitudes and Positive Predictions Inventory (Brief-HAPPI: Mansell & Jones, 2006). A 30 item self report measure that measures problematic beliefs about mood states bipolar mood states. Scores on the Brief-HAPPI have been found to be elevated amongst individuals with Bipolar Disorder; it is included as such beliefs have been hypothesised to potentiate unhelpful responses to extreme mood states in bipolar disorder (Mansell et al., 2006), and the current study provides an opportunity to explore whether this variable is associated with change in impulsive responses to mood and symptom change over the course of treatment.

Inventory of Interpersonal Problems – Short Version (IIP-32: Barkham, Hardy & Startup, 1996). A 32 item self report measure of interpersonal difficulties across eight domains. This short version has been found to have comparable psychometric properties to the established 127 item version, but places a lower burden on participants in terms of time to complete. This measure is included as interpersonal effectiveness is a key target of DBT.

*Intervention*

The intervention consists of 16 sessions of group skills training based upon DBT, supported by individual meetings of up to 30 minutes that occur approximately monthly for each person, immediately following the end of each group session. The original DBT protocol and materials have been adapted for use with individuals with Bipolar Disorder by the applicants, and have been used clinically within two previous groups. Feedback from clinicians and patients involved in these groups has been used to iteratively refine the protocol and materials. The current version of the group follows a modular format: participants complete these modules in the following order (mindfulness, emotion regulation, mindfulness, distress tolerance, mindfulness, interpersonal effectiveness, consolidation), however if a participant leaves the group early, another participant can take his / her place at the start of the next module. This helps to maximise the number of people that can take part in the group. We will run two cycles of the entire 16 week group, to allow us to adequately test the feasibility of an open group design (whereby some participants may have started midway through the first cycle of the group, thus require the opportunity to complete the modules they missed, during a second cycle). No new participants will be able to join the group later than the start of the “emotion regulation” module of the second cycle, to ensure that all participants have the opportunity to be exposed to all modules. The group will finish after the end of the second cycle, or after the last participant has completed all modules, whichever is sooner.

After the end of the first group, “reunions” will be held every 3 months until all participants in both groups have had the opportunity to attend at least one reunion. All participants who have finished treatment will be invited to these, and sessions will focus upon celebrating practice done by participants and gains made, and by supporting participants with recently difficulties through group consideration of how skills learned could be applied.

*Procedure*

Patient participants will be identified by staff members in the xxxxxxx Mental Health Assessment Team (with the xxxxxxx Assessment Team being a second possible recruitment source if necessary) on receipt of referrals of individuals with Bipolar Disorder. If necessary we will also recruit from Recovery services (secondary mental health teams) in Exeter. Participants likely to meet study criteria will be informed about the study by the assessing staff member during a routine assessment appointment (given Participant Information Sheet). If necessary the patient and / or staff member can liaise with the research team to address questions about the study and study eligibility that arise at this stage. Patients expressing an interest in the study will then be referred to the AccEPT service, which hosts the project. Once referred, potential participants will be contacted to explain the study, have an opportunity to answer questions, and arrange an assessment appointment if they wish to proceed. At the assessment appointment the researcher will explain the study further, address questions and take informed consent. Following this the researcher will ascertain whether the participant meets study inclusion / exclusion criteria (the SCID will be used to investigate criteria pertaining to diagnosis). If the participant is not eligible for the study this will be explained and the participant referred onwards as appropriate. If the participant is eligible he / she will be invited to complete the “outcome” and “process” measures listed above, in addition to the standard assessment measures used within the AccEPT service. This can be done in the University or at home, in accordance with the participant’s preference. The participant will also be asked to complete the ESM recording period for a week prior to starting the group. He / she will be instructed in the use of the app at the end of the assessment session.

Participants will then undertake treatment as per the usual procedures at the AccEPT service; this involves completing measures of symptoms (ASRM and BDI-II) at each session. To this we will add the single item measure of group fit, and a single visual analogue scale of mood that day (from -10 to +10).

In addition participants will complete the following measures half way through the group cycle: UPPS-P, KIMS, BADS, HAPPI, IIP-32.

At the end of treatment participants will complete the standard set of “exit” questionnaires for the AccEPT service plus the outcome and process measures and SCID mood disorders section for the period since initial assessment, and will return for an individual meeting (standard practice).

Participants will be followed up six months after the end of treatment when they will complete the BDI-II, ASRM, QoL.BD, BDRQ, acceptability and group fit questionnaires, as well as the SCID mood disorders section for the past six months.

Staff participants will be identified by the CI informing the teams concerned at a team meeting. Information sheets and consent forms will be distributed. Staff will be able to opt to complete either an anonymous questionnaire, an interview, or both. Questionnaires will be left at the team base for staff members to complete, and a researcher will return at a later date to collect the completed anonymous forms. For staff wishing to take part in the interview, they will be asked to contact the research team to discuss further. If he / she remains interested an appointment will be arranged either in person (in the staff member’s place of work, or at the University of Exeter) or over the telephone. This will take around 20 minutes. Staff will be asked to complete these on two occasions: before the first participant starts the Thrive programme, and after the final patient completes.

*Statistical Analysis*

In order to assess acceptability and feasibility descriptive statistics will be used to represent participant uptake and retention across the study. In addition, acceptability interview data will be presented in terms of descriptive statistics, and qualitative data will be subjected to thematic analysis.

Mean change in questionnaire scores will be assessed through presentation of descriptive statistics and use of non-parametric tests (paired sample Wilcoxon Signed Rank Test).

